### Safety outcomes

The safety of the investigational product will be measured by comparing the laboratory liver and renal function test results (AST, ALT, blood urea nitrogen, and creatinine) before and after intervention in each group. Investigators will also examine the adverse events through medical examinations and participant reports at each visit, and all adverse events during the study will be systematically recorded in the CRF regardless of the relationship with the intervention provided in this study. Investigators will ensure that all participants with adverse reactions receive adequate medical attention and follow-up until the symptoms are resolved.

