Drugs that can cause dramatic changes in the gut microbiome (such as antibiotics and lactic acid bacteria) should be used cautiously only if needed, to minimize the effect on the gut microorganism, which is an exploratory outcome measure of this study. For participants who are already taking lactic acid bacteria, the investigators will instruct them not to change the dose or type as much as possible during the trial. If there is any change, the investigators will record the details in the CRF.

The use of statins, ezetimibe, fibric acid derivatives, PCSK9 inhibitors, cholestyramine, nicotinic acid, omega-3 fatty acids, systemic steroids, diuretics, amiodarone, and cyclosporine, which can affect the lipid profile, and the use of drugs that can affect thyroid function such as thyroxine will be forbidden during the study period. However, the use of 4 g omega-3 fatty acids or less per day and short-term use of 6 mg or less per day of dexamethasone or equivalent corticosteroids within 5 days, which would not affect lipid levels [19, 20], are allowed.

Dietary content and the physical activity level of participants are factors that may affect the results of this trial. In addition, gut microflora is affected by recent dietary intake. Therefore, we will compare food intake and the degree of physical activity before and after 8-weeks of investigational product administration by using a 3-day food record and the validated Korean version of international physical activity questionnaire short form [22], respectively. Participants in both groups will be educated and instructed to follow dietary and exercise guidelines for hyperlipidemia using a brochure based on the Korean Guidelines for the Management of Dyslipidemia [4].

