### Sample size

This is the first study to explore the feasibility and lipid-improving effect and safety of HHT granules compared with placebo granules. Therefore, a formal sample size calculation is not required [26]. Based on a study recommending a minimum of 12 participants per group for a pilot study [27], we selected 15 participants per group as a sample size for this trial, considering a 20% dropout rate.

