### Statistical analysis

An independent statistician will conduct statistical analysis using SAS® Version 9.4 (SAS Institute Inc., Cary, NC). In principle, efficacy analysis will be conducted using a full analysis set according to the intention-to-treatment principle, including all randomly assigned participants receiving at least one evaluation after the investigational product has been prescribed at least once. If necessary, per protocol set (PPS) analysis will also be conducted including only participants who have completed the entire process as described in the protocol and have no significant violations. Participants less than 70% compliant with the investigational product will be excluded from the PPS analysis. Safety analysis will include all data obtained from participants who have taken at least one investigational product.

The demographic and general clinical characteristics of participants will be summarized by group. Continuous data will be presented as mean and 95% confidence intervals or median according to the distribution of the data and dichotomous data as frequency and percentage. Continuous data will be analyzed using the independent *t* test or Wilcoxon rank sum test, and dichotomous data will be analyzed using the chi-square test or Fisher’s exact test.

The primary outcome in this study is the mean change in LDL-C from baseline to week 8. A two-sided test with a significance level of 5% will be performed using an analysis of covariance with baseline as the covariate and the treatment group as the fixed factors. The intra-group changes of outcome measures from baseline to post-treatment will be analyzed using paired *t* test or Wilcoxon signed rank test for continuous variables and the chi-square test or Fisher’s exact test for dichotomous variables. Furthermore, repeated measures analysis of variance will be used to compare the differences in trends between visits in each group. Missing values will be replaced with the multiple imputation method. If necessary, a subgroup analysis can be performed by categorizing the participant’s initial characteristics at the screening or baseline visit.

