## Discussion

This is a study protocol for a randomized, double-blind, placebo-controlled, parallel, investigator-initiated, pilot clinical trial evaluating the effect of HHT on patients with hyperlipidemia. We will evaluate the preliminary efficacy and safety of 8-week administration of HHT compared with placebo granules and assess the feasibility of large-scale RCTs. According to the 2019 European Society of Cardiology and European Atherosclerosis Society Guidelines for the management of dyslipidemias, LDL-C analysis is recommended as the primary lipid analysis method for screening, diagnosis, and management [28]. Therefore, we set the inclusion criteria and primary outcome measure for our study as LDL-C, not TC or TG. In addition, we set 250 mg/dl as the upper bound for LDL-C in the inclusion criteria by referencing the guidelines for clinical trials for hyperlipidemia treatment by the Korean Ministry of Food and Drug Safety [29], considering that this study will include participants who are not taking conventional lipid-lowering drugs. According to a consensus document on clinical research in Chinese medicine, it is recommended to recruit participants according to the conventional medicinal diagnosis, and then to perform pattern identification before randomization. Recruiting participants based on pattern identification can be considered if a limited number of identifiable patterns exist [30]. To the best of our knowledge, there has been no consensus on standardized pattern identification for hyperlipidemia. Therefore, we will recruit hyperlipidemia participants according to the conventional medical diagnosis, and then perform cold-heat pattern identification before randomization.

Although there is a previously published clinical trial evaluating the efficacy and safety of HHT in hyperlipidemia, it directly compared HHT and Simvastatin, and the duration of treatment was 4 weeks [15]. Our study attempts to evaluate the efficacy of HHT compared to placebo in patients with hyperlipidemia who are not taking conventional lipid-lowering drugs such as statins, and the treatment period was set to 8 weeks. Therefore, there was no reference to calculate the formal sample size, and if this pilot study design is feasible, a confirmatory clinical trial will be conducted by calculating the appropriate sample size based on the results of this study.

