Recent studies have shown a close relationship between hyperlipidemia and gut microorganisms and patients with hyperlipidemia often exhibit intestinal microbiota disorders that might further impair lipid metabolism [40]. Recent research showed that *Berberine*, the main component of *Coptidis Rhizoma,* improves lipid metabolism in the liver by changing gut microbiota and by regulating bile acid metabolism and the farnesoid X receptor pathway in the intestine [41]. Therefore, we will investigate the changes in the gut microbiome before and after HHT administration and explore the effects of HHT on the composition, diversity, and species abundance of gut microorganisms in patients with hyperlipidemia.

Side effects from the use of HHT may include gastrointestinal reactions such as anorexia, stomach discomfort, nausea, and vomiting, and hypersensitivity reactions such as rash and urticaria. In rare cases, interstitial pneumonia or liver dysfunction may occur. However, according to related clinical trials in which HHT was administered to patients with hyperlipidemia, no serious adverse reactions were observed and no abnormalities were found in blood and urine tests and electrocardiograms [15, 42].

In our study, there is a limitation due to the small sample size of 15 participants per group and this may not be enough to draw a definite conclusion of the efficacy of intervention. However, to the best of our knowledge, this is the first RCT assessing the effect of HHT on patients with hyperlipidemia. If the treatment effect and safety of HHT compared with placebo granules is found to be promising in this study and the study design is feasible, we will design a confirmatory, large-scale RCT based on the results of the study to draw definitive conclusions regarding the efficacy of HHT.

In conclusion, this article presents the protocol for a rigorously well-designed, double-blind, placebo-controlled, pilot RCT on HHT for patients with hyperlipidemia. Our study has the strengths of using placebo granules as the control and using the objective blood lipid parameter, LDL-C, as the primary outcome, to minimize performance bias and detection bias. The findings of this study are expected to provide a base for large-scale, confirmatory RCT to confirm the efficacy and safety of HHT for the treatment of patients with hyperlipidemia. Additionally, stronger evidence of HHT as a treatment option for hyperlipidemia may be provided to clinicians, patients, and researchers.

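### Laboratory safety is described as a before-after comparison within each group, while the stated aim is safety compared with placebo

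*Protocol article*

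**What the plan says.** The Safety outcomes section of the protocol article sets laboratory safety as "comparing the laboratory liver and renal function test results (AST, ALT, blood urea nitrogen, and creatinine) before and after intervention in each group". It names no contrast between HHT and placebo for these four values.

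The aim is worded differently in three places:

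- The Sample size section calls this the first study to "explore the feasibility and lipid-improving effect and safety of HHT granules compared with placebo granules".
- The Discussion says "We will evaluate the preliminary efficacy and safety of 8-week administration of HHT compared with placebo granules".
- The Discussion later links a confirmatory trial to this comparison: "If the treatment effect and safety of HHT compared with placebo granules is found to be promising in this study".

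The Statistical analysis section contains four items that bear on the point:

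- LDL-C is compared between groups "using an analysis of covariance with baseline as the covariate and the treatment group as the fixed factors".
- Changes within a group are given paired tests (paired t or signed rank).
- One generic sentence reads "Continuous data will be analyzed using the independent *t* test or Wilcoxon rank sum test". It stands in the paragraph that opens with demographic and general clinical characteristics.
- The one sentence on safety analysis defines the population (everyone who took the product at least once) and names no comparison.

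The Interventions section adds a co-intervention for everyone: "Participants in both groups will be educated and instructed to follow dietary and exercise guidelines for hyperlipidemia using a brochure".

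**The concern.** A before-after change in one arm does not isolate the drug. It adds the HHT effect to whatever else moved the values over 8 weeks, such as time or the lifestyle advice given to both arms. The placebo arm is there to remove that common part, and the contrast stated for laboratory safety does not use it.

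Two errors become possible. A rise in liver enzymes caused by HHT could be offset by a fall shared with placebo, so that the HHT arm looks unchanged. Conversely, a shared rise could be read as an HHT effect. The liver values matter most here because the Discussion names a hepatic risk: "In rare cases, interstitial pneumonia or liver dysfunction may occur". The results are also meant to inform whether a larger trial follows.

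**Working it through.** **The plan's own figure.** The Sample size section gives a minimum of 12 per group and 20% dropout. 12 / (1 − 0.20) = 15 per group, 30 in total, which reproduces the stated size. The calculations below therefore use n = 15, with n = 12 for the case of full dropout.

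**The two contrasts.** Let d be the HHT effect on a laboratory value and c a fall common to both arms (negative c is a shared rise).

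- Expected HHT change: d − c
- Expected placebo change: −c
- Expected difference, HHT minus placebo: (d − c) − (−c) = d

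The HHT before-after change thus misses d by exactly the placebo-arm change, at any sample size. This step needs no assumption about tests or SDs.

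**Illustration.** The documents give no SD and no expected drift for AST, ALT, blood urea nitrogen or creatinine. The following are assumptions: normally distributed changes, SD of change s = 10 U/L (range 8 to 12), and the values of d and c shown. Probabilities come from the noncentral t distribution, with two-sided 95% intervals and no baseline adjustment.

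- Within HHT: noncentrality (d − c) / (s/√n), df = n − 1
- Between groups: noncentrality d / (s√(2/n)), df = 2n − 2

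For example, with n = 15, s = 10, d = 10 and c = 5, the within-group noncentrality is 5 / 2.582 = 1.94, and the between-group noncentrality is 10 / 3.651 = 2.74.

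Probability that the interval lies above zero, n = 15, s = 10 (range for s = 12 to 8):

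| Scenario (U/L) | Within HHT | Between groups |
|---|---|---|
| d = 10, shared fall 10 | 2.5% (any s) | 75% (60–91%) |
| d = 10, shared fall 5 | 44% (32–61%) | 75% (60–91%) |
| d = 0, shared rise 5 | 44% (32–61%) | 2.5% |
| d = 10, no shared change | 95% | 75% |

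With 12 per group, the first row becomes 2.5% against 65% (50–83%).

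Setting the two within-group results side by side does not repair this. In the third row each arm shows a significant change with probability p = 0.438, so exactly one arm does so with probability 2p(1 − p) = 2 × 0.438 × 0.562 = 0.49, although HHT does nothing. A simulation with 40,000 replicates gave the same results for that scenario: 0.436 within HHT, 0.492 for exactly one arm, 0.025 between groups.

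**Precision at s = 10.**

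- Within group: t(14) × 10/√15 = 5.54 at n = 15; t(11) × 10/√12 = 6.35 at n = 12
- Between groups: t(28) × 10 × √(2/15) = 7.48 at n = 15; t(22) × 10 × √(2/12) = 8.47 at n = 12

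**The case against.** The strongest reply is that the Safety outcomes section describes what is measured, and that the tests are set out under Statistical analysis. Quality of life and faecal samples are also described as taken before and after treatment, and nobody would read that as excluding a group comparison. The generic t test or rank sum line is not expressly limited to baseline variables. If it were, most secondary outcomes would also lack an explicit two-group test, which is unlikely to be the intention in a placebo-controlled trial. The article condenses a fuller protocol, and an analysis plan may add the comparison.

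This stands in part: the authors may well intend a between-group analysis. But the safety text goes beyond a measurement schedule. It says that safety is to be measured by a comparison, and it says which one. The generic line is not tied to safety, while the same section assigns paired tests to changes within groups, which matches the safety wording. The point is therefore a stated contrast that does not answer the stated aim, and not a missing detail.

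Three further objections stand in full:

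- All SDs and drifts above are assumed. The first row of the table needs a shared fall of a full SD that cancels the HHT effect exactly, and nothing was calculated for blood urea nitrogen or creatinine.
- With no shared change, the within-group comparison detects harm more often.
- Rare liver dysfunction would be found, if at all, through individual adverse events and not through means in 15 participants per group. Those events are recorded at each visit whatever their cause.

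**Conclusion.** The point holds as a mismatch between aim and contrast. Laboratory safety is stated as before versus after within each group; the aim in the Sample size section and the Discussion is safety against placebo. The within-group change differs from the HHT effect by the change common to both arms. That part rests on algebra alone.

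How much this matters in practice is unknown. The percentages illustrate what could happen under assumed values and do not predict this trial.

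Three stronger readings are not supported:

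- A reader might infer that the diet and exercise advice makes a shared change in these laboratory values likely. The documents do not say that the advice moves AST, ALT, blood urea nitrogen or creatinine, or in which direction.
- A reader might infer that a formal go/no-go decision rests on the wrong contrast. The Discussion sentence about promising results is narrative and sets no rule.
- A reader might infer that a group comparison of these values is ruled out. Nothing excludes one, and the generic test line could be read to cover it.

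Severity is low to moderate. Adverse-event recording is not affected.

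**What to change.** Replace the first sentence of the Safety outcomes section with wording such as: *Laboratory safety will be assessed in the safety set by comparing the change in AST, ALT, blood urea nitrogen and creatinine from baseline to the post-treatment visit between the HHT and placebo groups, as a baseline-adjusted difference with 95% confidence interval (analysis of covariance as for LDL-C; log scale if skewed). Changes within each group will be shown descriptively.* Add that the difference is read as an estimate through its interval, and that a non-significant result is not evidence of no liver or renal effect.

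This uses data already collected and a model already planned for LDL-C, and it leaves the sample size unchanged. The price is precision: if the SD of change is 10 U/L, the half-width grows from about 5.5 to 7.5 U/L at 15 per group, and from about 6.4 to 8.5 at 12 per group, before any gain from baseline adjustment. Keeping the within-group changes as description retains what they show if there is no shared change.

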### Sample size

This is the first study to explore the feasibility and lipid-improving effect and safety of HHT granules compared with placebo granules. Therefore, a formal sample size calculation is not required [26]. Based on a study recommending a minimum of 12 participants per group for a pilot study [27], we selected 15 participants per group as a sample size for this trial, considering a 20% dropout rate.

### Statistical analysis

An independent statistician will conduct statistical analysis using SAS® Version 9.4 (SAS Institute Inc., Cary, NC). In principle, efficacy analysis will be conducted using a full analysis set according to the intention-to-treatment principle, including all randomly assigned participants receiving at least one evaluation after the investigational product has been prescribed at least once. If necessary, per protocol set (PPS) analysis will also be conducted including only participants who have completed the entire process as described in the protocol and have no significant violations. Participants less than 70% compliant with the investigational product will be excluded from the PPS analysis. Safety analysis will include all data obtained from participants who have taken at least one investigational product.

The demographic and general clinical characteristics of participants will be summarized by group. Continuous data will be presented as mean and 95% confidence intervals or median according to the distribution of the data and dichotomous data as frequency and percentage. Continuous data will be analyzed using the independent *t* test or Wilcoxon rank sum test, and dichotomous data will be analyzed using the chi-square test or Fisher’s exact test.

The primary outcome in this study is the mean change in LDL-C from baseline to week 8. A two-sided test with a significance level of 5% will be performed using an analysis of covariance with baseline as the covariate and the treatment group as the fixed factors. The intra-group changes of outcome measures from baseline to post-treatment will be analyzed using paired *t* test or Wilcoxon signed rank test for continuous variables and the chi-square test or Fisher’s exact test for dichotomous variables. Furthermore, repeated measures analysis of variance will be used to compare the differences in trends between visits in each group. Missing values will be replaced with the multiple imputation method. If necessary, a subgroup analysis can be performed by categorizing the participant’s initial characteristics at the screening or baseline visit.

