### Efficacy outcomes

The primary outcome is the blood level of LDL-C, which will be measured at baseline and 4, 8, and 12 weeks after randomization. In this study, the primary endpoint is 8 weeks post-treatment. The secondary outcomes are other blood lipid parameters including TC, TG, HDL-C, non-HDL-C, non-HDL-C/HDL-C, apolipoprotein (Apo) A1, Apo B, Apo B/Apo A1, lipoprotein (a), and atherogenic index of plasma (Log(TG/HDL-C), and atherosclerosis biomarkers including high-sensitivity C-reactive protein (hs-CRP), fibrinogen, and homocysteine, which will be measured at baseline and 4, 8, and 12 weeks after randomization. Using VP-1000plus (OMRON Healthcare Co., Kyoto, Japan), the degree of vessel hardening will be assessed through brachial-ankle pulse wave velocity (baPWV). The degree of narrowing due to vascular lesions will be assessed by measuring the blood pressure difference between the ankle and arm using the ankle-brachial index (ABI) to determine the degree of arteriosclerosis. Blood glucose parameters including fasting glucose and HbA1c, blood pressure, and anthropometric parameters including body weight, body fat percentage, body fat mass, skeletal muscle mass, waist circumference, hip circumference, and waist-to-hip ratio will also be measured. The health-related quality of life before and after taking the investigational product will be measured using the five-level EuroQol-5 dimensions (EQ-5D-5L). The EQ-5D-5L is composed of 25 items in five domains including mobility, self-care, usual activities, pain/discomfort, and anxiety/depression. Participants will respond to each item with five response levels: no problems (level 1), slight, moderate, severe, and extreme problems (level 5) [23]. The Korean version of EQ-5D–5 L will be used after permission from the EuroQol Research Foundation. Blood lipid parameters, atherosclerosis biomarkers, the degree of arteriosclerosis, blood glucose parameters, blood pressure, anthropometric parameters, and EQ-5D-5L will be measured at baseline and 4, 8, and 12 weeks after randomization.

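### Baseline-adjusted ANCOVA is specified only for LDL-C; the one simple between-group test named for other continuous data is unadjusted, and its scope is unclear

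*Protocol article*

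**What the plan says.** All analysis wording is in the Statistical analysis section of the protocol article.

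- **Primary outcome.** "The primary outcome in this study is the mean change in LDL-C from baseline to week 8". The model follows at once: "A two-sided test with a significance level of 5% will be performed using an analysis of covariance with baseline as the covariate", with treatment group as the other term. No sentence extends this model to another outcome.
- **Other continuous data.** The preceding paragraph opens with "The demographic and general clinical characteristics of participants will be summarized by group" and goes on to say "Continuous data will be analyzed using the independent *t* test or Wilcoxon rank sum test". It does not name the variables, or say whether follow-up values or changes are tested.
- **Within-arm analysis.** "The intra-group changes of outcome measures from baseline to post-treatment will be analyzed using paired *t* test or Wilcoxon signed rank test".
- **Repeated measures ANOVA.** This is planned for trends across visits, described group by group. No outcomes are listed, and the text does not say whether baseline counts as one of the visits.

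The Efficacy outcomes section shows that baselines exist. LDL-C, the other lipids and the atherosclerosis biomarkers "will be measured at baseline and 4, 8, and 12 weeks after randomization". The same schedule is given for arterial stiffness and ABI, glucose parameters, blood pressure, anthropometry and EQ-5D-5L. The cold-heat questionnaire and the exploratory microbiome samples are taken at baseline and week 8.

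**The concern.** Each of the two readings of the t test/Wilcoxon sentence leaves a weakness.

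- **General rule.** The secondary outcomes are compared without a covariate that is measured in everyone and that the plan already uses for LDL-C. Randomisation is unstratified and only 30 people enter, so chance baseline differences on some of the many secondary outcomes are to be expected. A comparison of week-8 values carries such a difference forward in proportion to the baseline correlation. A comparison of changes over-corrects when that correlation is low.
- **Baseline characteristics only.** The plan then tests for differences between randomised arms before treatment, where any difference is due to chance by design. For the secondary outcomes, what remains in the text is paired tests within each arm and the loosely described repeated measures ANOVA. Within-arm change is not the comparison that a placebo group is there to provide.

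At stake are the width of the confidence intervals for secondary outcomes and clarity about which analysis will be reported. The Discussion says a confirmatory trial would be designed from this study's results, so precise between-arm estimates are useful.

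**Working it through.** **Plan's own figure.** The Sample size section gives a minimum of 12 per group and 20% dropout. 12 / (1 − 0.20) = 15 per group, 30 in total, which matches the plan. The two sizes used below are therefore 15 (all randomised) and 12 (after the planned dropout).

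**Inputs from the document.** n = 15 or 12 per arm, 1:1 allocation, and 5% two-sided (stated for the primary outcome and used here for illustration).

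**Assumed inputs.** The document gives no baseline-to-week-8 correlation r, so r is varied. Equal SDs at baseline and week 8 are assumed, and results are in units of that SD. For power only, a true difference of 0.8 SD is assumed.

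**Variance of the estimated difference, as a multiple of 2·SD²/n**

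- t test on week-8 values: 1
- t test on change: 2(1 − r)
- ANCOVA: (1 − r²)(1 + 1/(2n − 4)); the last factor is the small-sample cost of estimating the slope

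The 95% CI half-width is t(0.975, df) × √(2 × multiple / n), with df = 2n − 2 for the t tests and 2n − 3 for ANCOVA.

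**Worked case, n = 15, r = 0.7**

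- Week-8 values: √(2/15) = 0.365; × 2.048 = 0.748
- Change: multiple 0.60; √(2 × 0.60/15) = 0.283; × 2.048 = 0.579
- ANCOVA: multiple 0.51 × (1 + 1/26) = 0.530; √(2 × 0.530/15) = 0.266; × 2.052 = 0.545

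A simulation of 20,000 trials gave standard errors of 0.364, 0.283 and 0.266 for this case.

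**Half-widths at 15 per arm, in SD units**

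| r | week-8 t test | change t test | ANCOVA | narrower than week-8 | narrower than change |
|---|---|---|---|---|---|
| 0.3 | 0.748 | 0.885 | 0.728 | 3% | 18% |
| 0.5 | 0.748 | 0.748 | 0.661 | 12% | 12% |
| 0.7 | 0.748 | 0.579 | 0.545 | 27% | 6% |
| 0.8 | 0.748 | 0.473 | 0.458 | 39% | 3% |
| 0.9 | 0.748 | 0.335 | 0.333 | 55% | under 1% |

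**Where the gain vanishes.** For r from 0 to 0.2, ANCOVA gives no gain over the week-8 t test (CI ratio 1.00 to 1.02 at 15 per arm, 1.01 to 1.03 at 12). At 12 per arm and r = 0.9, ANCOVA and the change-score test have the same half-width, 0.379.

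**Power at 12 per arm, r = 0.7, difference 0.8 SD**

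- Week-8 t test: SE = √(2/12) = 0.408; noncentrality 0.8/0.408 = 1.96; 22 df; power 47%
- Change t test: SE = √(2 × 0.60/12) = 0.316; noncentrality 2.53; 22 df; power 68%
- ANCOVA: multiple 0.51 × (1 + 1/20) = 0.5355; SE = √(2 × 0.5355/12) = 0.299; noncentrality 2.68; 21 df; power 72%

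**The case against.** The case for leaving the text alone has several parts.

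1. **Scope of the sentence.** A reader might infer that the plan assigns unadjusted tests to all secondary outcomes. The text does not say so. The sentence stands in the paragraph on demographic and clinical characteristics, and outcome analysis begins in the next one. This stands: the scope is ambiguous, and the loss of precision applies only if the sentence is a general rule.
2. **Matters left to fuller documents.** The article condenses a full protocol, and an analysis plan may exist. Silence on per-outcome models is therefore no fault. This is correct, but the point here is a test that is stated with undefined scope beside an adjusted model tied to one outcome.
3. **Repeated measures ANOVA.** It might serve as a between-arm analysis and use baseline as a visit. That is possible. As worded, it neither says so nor clearly yields a baseline-adjusted difference between arms.
4. **Choice of test.** A reader might infer that the plan picks t or Wilcoxon from the observed distribution. The remark about distribution is attached to how data are presented (mean or median). No rule for choosing the test is given, so a data-driven choice cannot be charged to the plan.
5. **Size.** The largest gains need a comparison of raw week-8 values, whereas the plan defines its primary outcome as a change. Against change scores the gain is small once r reaches 0.7. This stands.
6. **Consequence.** This is a pilot without a formal power calculation, it acknowledges its small size, and its primary outcome is already adjusted. Nothing says that secondary outcomes will drive the size of the next trial. This also stands.

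**Conclusion.** The point holds as a matter of precision and clarity. ANCOVA is fixed for LDL-C only, the one simple between-group test named for other continuous data is unadjusted and of unclear scope, and the baselines needed to do better are already collected.

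How much is lost depends on a correlation and a scale of analysis that the document does not give. The main reason to prefer ANCOVA is that it does well across the range: the week-8 test is poor when r is high and the change-score test is poor when r is low. The contrast of 47% with 72% power at 12 per arm is the unfavourable end. It requires raw week-8 values, r = 0.7 and a difference of 0.8 SD, all assumed; against change scores the contrast is 68% with 72%.

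A reader might infer that the secondary results would be biased or that the trial's main conclusion is at risk. Neither follows. An unadjusted comparison of randomised arms is unbiased, and the LDL-C analysis does not depend on this sentence. The change is worthwhile and free, but the trial's validity does not hang on it.

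**What to change.** In the Statistical analysis section, or in the analysis plan before unblinding:

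- State that each continuous secondary outcome is compared between arms by ANCOVA with its own baseline as covariate and treatment group as factor, reported as an adjusted difference with 95% confidence interval.
- Prespecify a log scale for skewed measures such as TG and hs-CRP. The plan already uses a log scale for the atherogenic index.
- Limit the t test/Wilcoxon sentence so that it no longer reads as the rule for outcomes that have a baseline.
- Summarise baseline characteristics by arm descriptively, without significance tests.
- Say which outcomes the repeated measures ANOVA covers, whether baseline is one of its visits, and whether it compares arms.

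The cost is wording only. No visit, measurement or participant is added, because every baseline value needed is already scheduled.
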